#### 2.14.2. Evaluation of the Secondary Aim

We will use the following statistical approaches to explore the preliminary efficacy of P3-EX to improve patient PA levels, CVD risk factors, and exercise adherence. A one-way Analysis of Variance will test if pre-intervention values are equal between groups, indicating if there is a need to adjust for potential covariates related to demographics, medication use, and/or pre-intervention PA level and CVD risk factor values. We will use a repeated measures two-way Analysis of Covariance using a linear mixed effects model to test patient differences in PA level and CVD risk factor changes over 12 weeks between the P3-EX and the PAVS groups, adjusting for potential covariates related to demographics, medication use, and/or pre-intervention values.

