#### 2.8.5. Blood Lipid-Lipoproteins and Glucose

Fasting laboratory assessments will be conducted by phlebotomy technicians and processed at convenient Quest Patient Service Centers. Patient total cholesterol, triglycerides, high-density lipoproteins, low-density lipoproteins (mg/dL), glycated hemoglobin (%), and fasting plasma glucose (mg/dL) will be assessed at pre- and 12 weeks post-intervention [41,42].

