#### 2.8.6. Subjective PA Levels and Exercise Adherence

Patient self-reported PA levels will be assessed at pre-intervention, and weekly for the 12-week exercise intervention via the TLFB-E. The TLFB-E is a validated calendar diary method [49] for recording the FITT of exercise, whereby, frequency is the number of days per week that PA is performed; type is the modality of PA performed (e.g., walking, lifting weights); time is the duration of each session performed in minutes for each modality; and intensity will be assessed using the Borg 6–20 rating of perceived exertion scale [60]. [name] and RAs will cross reference self-reported frequency, intensity, and time values on the TLFB-E with the 2024 Adult Compendium of Physical Activities [61] and accelerometer data to determine the agreement and verify atypical or unrealistic values. For each recorded PA, [name] and RAs will assign a metabolic equivalent value from the PA compendium to calculate the PA volume performed (MET·min/wk).

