#### 2.8.7. Objective PA Levels

Patient energy expenditure (kcal), steps per day, sedentary behavior (minutes/wk) and light, moderate, and vigorous intensity PA (minutes/wk) [49] will be measured at pre- and 12 weeks post-intervention via accelerometers (ActiGraph wGT3X-BT, ActiGraph Corp., Pensacola, FL, USA) [62]. [name] and an RA will instruct patients to wear the accelerometer using an elastic strap with placement aligned on the hip/anterior iliac crest of their nondominant hand side except when swimming, bathing, showering, or sleeping. The ActiLife6 full version software (version 6.0, ActiGraph Corp., Pensacola, FL, USA) [63] will be used to initialize and download accelerometer data. [name] will verify complete accelerometer data, defined as having ≥60% of wear time during waking hours on four consecutive days including two weekends and two weekdays. Waking hours will be calculated based on the reported sleep hours on the TLFB-E. If patients have incomplete data, they will be asked to re-wear the accelerometer for a second attempt.

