### 2.14. Statistical Analysis

The statistical analysis plan for this trial is accessible on ClinicalTrials.gov. Statistical analyses will be conducted by [name] using Statistical Package for the Social Sciences (version 30, IBM Corp., Armonk, NY, USA) [74] with oversight from [name], [name], [name], [name], and [name], with [name], [name], [name], and [name] being blinded to group assignments. We will first use descriptive statistics and graphical techniques to ensure all test assumptions are met, including the inspection for outliers, normal distributions [75], and homogeneity of variances [76]. Missing values will be addressed using model-based approaches and/or multiple imputations when appropriate to include the entire randomized sample [77]. If normality assumptions are not met for secondary outcomes, considerations will be made to transform the data to achieve a normal distribution or use alternative non-parametric approaches such as permutated tests. An alpha level of 0.05 will be used to determine statistical significance.

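### A significance test on pre-intervention values decides whether the patient comparison is adjusted; adjustment for each outcome's own pre-value should be fixed in advance instead

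*Protocol article*

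**What the plan says.** Section 2.14.2 of the protocol article sets out the patient analysis in two steps. A one-way ANOVA "will test if pre-intervention values are equal between groups, indicating if there is a need to adjust for potential covariates". The second step names the model: "We will use a repeated measures two-way Analysis of Covariance using a linear mixed effects model". Its target is the contrast in "PA level and CVD risk factor changes over 12 weeks between the P3-EX and the PAVS groups". The covariates are left conditional, the wording being "adjusting for potential covariates related to demographics, medication use, and/or pre-intervention values". Section 2.14 sets the level: "An alpha level of 0.05 will be used to determine statistical significance".

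Most of these outcomes have two time points. Lipids and glucose "will be assessed at pre- and 12 weeks post-intervention", and accelerometer outcomes "will be measured at pre- and 12 weeks post-intervention via accelerometers". The cardiovascular health score, blood pressure, heart rate and body measures (2.8.2 to 2.8.4) follow the same schedule. The diary is the exception: "Patient self-reported PA levels will be assessed at pre-intervention, and weekly for the 12-week exercise intervention via the TLFB-E".

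**The concern.** A test of baseline equality is a poor guide to whether to adjust. Under random allocation the null hypothesis is true, so a significant result is a chance finding. A non-significant result does not mean that the observed imbalance is harmless. The value of adjusting comes from how well the pre-value predicts the 12-week value, and the ANOVA does not measure that. If the rule is applied outcome by outcome, some outcomes will be adjusted and others not, depending on the data.

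What is at stake is precision and a prespecified model in a small comparison (24 per arm recruited, 19 per arm planned to complete). The conclusions (section 5) say the secondary-outcome data will be used to power a larger trial, so the quality of these estimates has a later use.

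**Working it through.** **Inputs from the article.** 38 patients to complete (19 per arm), 48 recruited (24 per arm), alpha 0.05. Sidedness is not stated; two-sided is assumed. The pre-post correlation r is not given and is assumed to be 0.5, 0.7 or 0.8. SDs are taken as equal at both times and set to 1. Clustering by physician is not modelled.

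**The plan's own figure.** Section 2.13 sizes the trial only for the primary physician test. Effect size: (4.650 − 4.0)/0.759 = 0.856. With one-sided alpha 0.01 and n = 19, power is 0.868 for a t-test, or 0.848 with the Wilcoxon efficiency 3/π under normality. This agrees with the stated 85%. Attrition: 19/0.8 = 23.75, so 24; 38/0.8 = 47.5, so 48. The figure reproduces. No power or precision is stated for the patient comparison.

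**Step 1: how the baseline test behaves.**
- Under randomisation it is significant at its own level, about 5% of the time (simulated 4.9 to 5.2%). In about 95% of outcomes it would say no adjustment is needed.
- Power for a true 0.5 SD difference (noncentral t, noncentrality 0.5·√(n/2)): 0.323 at 19 per arm, 0.396 at 24.
- Smallest observed difference that reaches significance, t-critical·√(2/n): 2.028 × 0.324 = 0.66 SD at 19 per arm; 2.013 × 0.289 = 0.58 SD at 24.
- Chance that the observed imbalance exceeds 0.4 SD and the test is still non-significant: about 17% at 19 per arm, 12% at 24 (simulated).

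**Step 2: what the group-by-time term estimates with two time points.** Write the mean as a + b·G + c·T + d·G·T + e·X, where G is arm, T is 0 (pre) or 1 (12 weeks) and X is the pre-value. Subtracting the T = 0 line from the T = 1 line leaves c + d·G. The e·X term cancels, so d is the between-arm difference in mean change with or without X. Fits to simulated data confirm that the two estimates are identical. If a significant ANOVA led to X being added in this form, the contrast would not move.

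**Step 3: precision.** Per-patient variance is 2(1−r) for a change score and 1−r² for the 12-week value adjusted for the pre-value. The ratio is 2(1−r)/[(1−r)(1+r)] = 2/(1+r). Estimating the slope multiplies the ANCOVA variance by 1 + 1/(2n−4), which is 1 + 1/34 = 1.029 at 19 per arm.

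| Assumed r | Change score vs always adjusting, 2/(1+r) | Same, 19 per arm (÷1.029) | Proper ANCOVA only when the test is significant, 19 per arm (simulated) |
|---|---|---|---|
| 0.5 | 1.33 | 1.30 | 1.22 |
| 0.7 | 1.18 | 1.14 | 1.11 |
| 0.8 | 1.11 | 1.08 | 1.06 |

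The columns for the change score and the last column rest on different readings and cannot both describe the plan. The change-score columns apply if nothing is added, or if the pre-value is added as in step 2. The last column applies if a significant test led instead to a model of the 12-week value on arm and pre-value.

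**Step 4: in terms of patients and power.** At r = 0.5, 38 completers are worth 38/1.333 = 28.5. For an effect that gives the adjusted analysis 80% power (0.842 + 1.960 = 2.802 standard errors), the change score has Φ(2.802/√1.333 − 1.960) = Φ(0.466) = 68%. At r = 0.8 it has Φ(2.802/√1.111 − 1.960) = Φ(0.698) = 76%.

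**The case against.** **The comparison is exploratory.** It is a secondary aim, framed as preliminary efficacy and trends. The change-score contrast is unbiased under randomisation, and at r = 0.8 the loss is only 6 to 11% of variance depending on the reading. All of this stands and limits the weight of the point. It does not justify the test, because always adjusting uses data already collected and is available at almost no cost.

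**The statistical analysis plan may say more.** It may, but the article does not leave this open. It states a decision rule, and the rule itself is the problem.

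**A stronger reading: the model uses the pre-value as both outcome and covariate.** A reader might infer this from the mention of pre-intervention values among the covariates. The text does not support it as a fixed feature. The covariates are described as potential and joined by and/or, so the pre-value is permitted, not required. If the ANOVA governs, the pre-value would enter for about 5% of outcomes, so the double role and the missing adjustment belong to different branches. For diary activity the concern need not arise at all: with weeks 1 to 12 as outcomes, a pre-value covariate is orthodox.

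**Baseline differences may not be pure chance.** Physicians pick the candidates (2.4) and learn their assignment once the first patient is enrolled (2.5.2), so the second patient may be chosen with the arm known. That is a reason to report baseline values and adjust for them throughout. A test with 32 to 40% power would not reliably reveal such selection.

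**Conclusion.** The point holds for the baseline test. Section 2.14.2 ties adjustment to a significance test that is significant for about 5% of outcomes under randomisation, and it lets the covariate set vary with the data. For outcomes with two time points the usual result is a change-score contrast. Its variance is about 8 to 30% above that of an always-adjusted analysis at 19 per arm, for r from 0.8 to 0.5. If a significant test led to a proper ANCOVA, the excess would be about 6 to 22%.

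These sizes depend on the assumed r, equal SDs at the two times and independent patients. The baseline-as-outcome-and-covariate problem is no more than an ambiguity to clear up for the two-time-point outcomes. The primary test, its sample size and the feasibility decision are unaffected. The change is worth making before data are analysed, but the trial's validity does not turn on it.

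**What to change.** - Delete the one-way ANOVA of pre-intervention values as a rule for adjustment. Describe baseline values by arm without p-values.
- For every outcome measured only before the intervention and at 12 weeks, model the 12-week value on arm with that outcome's own pre-intervention value always included. Any demographic or medication covariate that is kept should be named in advance, not chosen after looking at baseline differences.
- For diary activity, use the weekly values as repeated outcomes with the pre-intervention value as a covariate.
- Do not offer a longitudinal model that constrains the arms to a common baseline mean as an equivalent. It relies on equal baseline expectation, which is doubtful where the second patient may be chosen with the arm known.

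Cost: wording in section 2.14.2 and the matching text of the statistical analysis plan, and one degree of freedom per model. No new data are needed.

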## Abstract

**Background:** Approximately half of U.S. adults have ≥1 cardiovascular disease (CVD) risk factors. Exercise is universally recommended as a first-line lifestyle therapy to prevent and treat CVD. **Objective:** We will conduct a feasibility and pilot efficacy randomized controlled trial to test the usability and user satisfaction of an evidence-based digital health tool we developed for physicians—the *P*rioritizes *P*ersonalizes *P*rescribes *EX*ercise algorithm (P3-EX)—to treat patients with CVD risk factors (ClinicalTrials.gov: NCT07238556). **Methods:** We will recruit 24 physicians who do not prescribe written exercise prescriptions (ExRx) from two local CT hospitals. Physicians will recruit two patients each (N = 48); both patients must have CVD risk factors. Each physician will deliver a P3-EX ExRx to one patient (n = 24) and the Physical Activity Vital Sign ExRx to the other patient (n = 24) in a random sequence crossover design. Physicians and patients will rate the feasibility and acceptability of each ExRx method using validated questionnaires. Patients will perform their ExRx for 12 weeks and complete an exercise diary to monitor exercise adherence with weekly virtual oversight by Research Assistants. Before and after the exercise intervention, we will measure patient CVD risk factors and physical activity levels via accelerometry. **Results:** This trial has received Institutional Review Board approval (E-HHC-2025-0198) and will begin in January 2026, with findings published in 2027. **Conclusions:** This protocol provides the scientific rationale and methodology to test P3-EX within a real-world clinical setting, to inform the feasibility of using P3-EX as a digital health support tool by physicians, and preliminary efficacy of P3-EX to improve patient cardiovascular health and physical activity levels.

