### 2.1. Trial Design

The P3-EX Feasibility Trial is a feasibility and pilot efficacy RCT with a two-arm crossover exploratory design (Figure 1). Physicians (N = 24) will be individually randomized with a 1:1 allocation ratio to deliver P3-EX to one of their patients (n = 24) and PAVS to another patient (n = 24) in random sequence. Because physicians will deliver P3-EX and PAVS to patients during their routine healthcare appointments that are scheduled in advance of their enrollment, we will not implement a washout period for physicians between their delivery of P3-EX and PAVS, but will control for potential period or carryover effects in statistical analyses.

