### 2.6. Interventions and Comparators

Each patient will attend their scheduled healthcare appointment with their physician and receive their healthcare as planned and permitted. During each appointment, in random sequence, the physician will deliver P3-EX to one patient and PAVS to the other patient.

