### 2.13. Sample Size Estimation

We conducted a power analysis using G*Power (version 3.1.9.6, Heinrich Heine University Düsseldorf, Düsseldorf, Germany) [68] to obtain a conservative usability rating of P3-EX to evaluate the primary aim of the study. We obtained the lowest observable usability score of 4.650 ± 0.759 (mean ± SD) converted from our feasibility survey study pilot data [32] to compare to the null hypothesis middle score of 4.0 on the mHealth Application Usability Questionnaire [50]. Using a one-sided Wilcoxon signed-rank (one sample case) test [69] at the significance level (α) of 0.01 and calculated effect size between the observed and middle score of Cohen’s d = 0.856, we determined that 19 physicians are required to achieve 85% power. Therefore, we will use 19 physicians to achieve 85% power (α of 0.01), and recruit two patients per physician to complete 38 patients. Using an observed attrition of 20% for patients in the study [70,71,72,73], this trial will aim to recruit 24 physicians and 48 patients (24 patients per group). Because physicians’ PA levels could influence how they perceive and rate the delivery of an ExRx [45], we aim to recruit half of the physicians who meet PA guidelines (n = 12) [44] and half who do not (n = 12).

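### The patient efficacy model lists no physician or delivery-order term, although each physician supplies one patient to each arm in randomised order

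*Protocol article*

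**What the plan says.** **Design.** Under section 2.1 of the protocol article, physicians "will be individually randomized with a 1:1 allocation ratio to deliver P3-EX to one of their patients" and PAVS to another, in random sequence. Section 2.6 repeats that "the physician will deliver P3-EX to one patient and PAVS to the other patient". Section 2.5.1 randomises the delivery sequence in permuted blocks of four within two physician activity strata. Under section 2.4 the physician picks both patients from their own upcoming appointments. Section 2.13 plans 24 physicians and 48 patients, 24 per group.

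**Period and carryover.** Section 2.1 sets no washout and says that possible period or carryover effects will be controlled in the statistical analyses. Section 4.2 repeats this as a strength. Neither sentence limits it to the physician ratings.

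**Analysis.** For the physician ratings, section 2.14.1 names delivery order, time between deliveries and their interaction. For the patients, section 2.14.2 first runs a one-way ANOVA of baseline values between groups to judge whether covariates are needed. It then compares "PA level and CVD risk factor changes over 12 weeks between the P3-EX and the PAVS groups" by a two-way repeated measures ANCOVA fitted as a linear mixed model. The adjusters named are demographics, medication and baseline values. The random effects are not named.

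**The concern.** Each physician is a block of two patients, one per arm, who share a selector, a practice and a person delivering the prescription. An analysis that follows the randomisation would carry that block and the position of the patient within it (first or second). The list in section 2.14.2 has neither, while section 2.14.1 does carry order for the physician outcomes. The commitment in section 2.1 is therefore spelled out for one half of the trial only, although a physician's second patient is the one who would receive any carryover in delivery.

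At stake is the accuracy of the standard errors and confidence intervals for the patient outcomes. Section 5 intends to use these data to power a larger trial.

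**Working it through.** **The plan's own figures.** Section 2.13 gives d = (4.650 − 4.0)/0.759 = 0.856 for a "one-sided Wilcoxon signed-rank (one sample case) test [69] at the significance level (α) of 0.01". With the asymptotic relative efficiency method (normal parent), 19 physicians give 84.75% power, which matches the stated 85% to rounding. Attrition: 19/0.8 = 23.75, so 24 physicians; 38/0.8 = 47.5, so 48 patients. These figures concern the physician rating and do not depend on the present point. No sample size is stated for the patient comparison.

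**Inputs for the check.** There are 24 pairs (section 2.13), and attrition follows "Using an observed attrition of 20% for patients in the study". The within-physician correlation ρ of the 12-week outcome after baseline adjustment is not in the document; it is assumed here over a range. Standard errors are in units of the residual SD. Tests are taken as two-sided at 5%, because section 2.14 gives the 0.05 level but no sidedness for this comparison.

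**Complete pairs.**
- Physician ignored: SE = √(2/24) = 0.289.
- Pairing used: SE = √(2(1 − ρ)/24).
- Ratio: 1/√(1 − ρ).

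**With attrition.** If losses are independent between patients, 24 × 0.8 × 0.8 = 15.36 pairs stay complete, and 24 × 0.8 × 0.2 = 3.84 unpaired patients remain in each arm. A mixed model that keeps the unpaired patients has variance 2/(15.36/(1 − ρ) + 3.84), against 2/19.2 if physician is ignored. At ρ = 0.10 this is 2/20.91, SE 0.309, against 0.323: a ratio of 1.043.

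**Degrees of freedom.** In a simple comparison with 24 pairs, the paired analysis has 23 df (t = 2.069) and the unpaired one 46 df (t = 2.013). The ratio of confidence interval widths, paired to unpaired, is 2.069 × √(1 − ρ)/2.013.

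Type I error and power come from 200,000 simulated trials per ρ with 24 complete pairs; power is for an assumed difference of 0.8 SD.

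| Assumed ρ | Paired SE | SE overstated, complete pairs | SE overstated, 20% attrition | Actual type I error if physician ignored | CI width, paired/unpaired | Power, unpaired vs paired |
|---|---|---|---|---|---|---|
| 0.05 | 0.281 | 2.6% | 2.1% | 4.5% | 1.002 | 78% vs 78% |
| 0.10 | 0.274 | 5.4% | 4.3% | 3.9% | 0.975 | 79% vs 80% |
| 0.20 | 0.258 | 11.8% | 9.5% | 2.9% | 0.919 | 80% vs 84% |

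**Where a physician term has to sit.** In a pre/post model the group-by-time contrast is built from within-patient changes. A physician intercept that is constant over time is subtracted out of each change, so adding only that term would barely alter the result. It has to act on the 12-week value adjusted for baseline, or vary with time.

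**How well ρ can be estimated.** In simulation with 24 complete pairs and true ρ = 0.10, the estimate ranges from about −0.3 to 0.5 (95% range) and is zero or below about 32% of the time. At true ρ = 0.05 that share is about 41%.

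**The case against.** The strongest reply is that section 2.14.2 specifies a mixed model without naming its random effects. A physician effect is compatible with that wording, and the SAP, which section 2.14 places on ClinicalTrials.gov and which is not at hand, may contain it. Section 2.14.1 names no physician random effect either. The general statement in section 2.1 could be read as already covering the patient analysis.

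Much of this stands. A reader might infer that the main patient model treats the two arms as independent, but the article does not say so; only the baseline one-way ANOVA is by its form an independent-groups test. A reader might also fear inflated false positives, but for positive ρ the type I error falls below 5%. Nor is ignoring a ρ of 0.10 the same as discarding a tenth of the patients: that equivalence assumes complete pairs and ignores the lost degrees of freedom, after which the interval narrows by only 2.5%. Finally, the document does not show that the larger trial will need this correlation, since section 5 does not say that it would pair patients within physician.

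What the reply does not remove is the mismatch within the article. Section 2.14.2 gives a list of adjusters, and that list leaves out the order term which sections 2.1 and 4.2 lead one to expect and which section 2.14.1 supplies for the other outcomes.

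**Conclusion.** The point holds in a limited form. The patient model as listed does not carry the physician block or the delivery order, and so does not match the design or the statement on period control in section 2.1. If the physician effect is in fact omitted, standard errors are too large by roughly 2% to 12% for assumed correlations of 0.05 to 0.20, depending on attrition. The error is conservative, affects an exploratory aim, and leaves the primary test and the sample size unchanged. The size rests on the assumed range of ρ, on ρ being positive, and, for the attrition figures, on independent losses. Correcting it is worthwhile mainly because the analysis would then follow the randomisation at almost no cost; the gain in precision is secondary.

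**What to change.** In section 2.14.2:

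- Model each 12-week patient outcome adjusted for its baseline value, with group, a random effect for physician and a fixed effect for first or second patient. If the pre/post repeated measures form is kept, let the physician effect vary with time.
- Keep patients whose pair-mate is lost; the mixed model allows this.
- Do not use the independent-groups baseline ANOVA to decide on adjustment; fix the covariates in advance.
- Report the within-physician correlation with its confidence interval, which will be wide.

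The cost is a sentence or two and a few degrees of freedom. At a correlation near 0.05 or below there is little or no gain in precision, and intervals may be slightly wider. A physician variance estimated at zero would not restore the analysis as now listed, because the order term remains.
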